### Flopropione Treatment

Flopropione (80 mg per tablet) will be administered orally 30 minutes before cisplatin initiation. Doses are as follows: 80 mg in cohort 1, 160 mg in cohort 2, and 240 mg in cohort 3. A second dose of the same amount will be given at least 4 hours later on day 1, followed by 80 mg 3 times daily on day 2 at intervals of at least 4 hours.

### Blood and Urine Collection

Blood and urine samples will be collected at the time points defined as the secondary and exploratory end points. The details of each test item are summarized in Table 2.

**Table 2 table2:** Laboratory test items.

Classification	Items
Hematological tests	White blood cell count, neutrophil count, lymphocyte count, monocyte count, eosinophil count, basophil count, red blood cell count, hemoglobin, hematocrit, and platelet count
Blood biochemical tests	Total cholesterol, triglycerides, total protein, albumin, albumin/globulin ratio, blood urea nitrogen, uric acid, creatinine, total bilirubin, aspartate aminotransferase, alanine aminotransferase, γ-glutamyl transpeptidase, alkaline phosphatase, lactate dehydrogenase, creatinine kinase (creatine phosphokinase), calcium, phosphorus, sodium, potassium, chlorine, and C-reactive protein
Urinalysis	Hematuria, glucose, protein, creatinine, neutrophil gelatinase-associated lipocalin, liver-type fatty acid-binding protein, kidney injury molecule-1, *N*-acetyl-β-d-glucosaminidase, β2-microglobulin, and α1-microglobulin

### Biomarker Measurements

The collected urine samples will be centrifuged at 400×*g* or higher for 5 minutes. Thereafter, the supernatants will be stored at –80 °C until analysis. The samples will be sent to LSI Medience Corporation for N-GAL, L-FABP, KIM-1, NAG, β2-microglobulin, and α1-microglobulin measurement. N-GAL will be measured by a chemiluminescent immunoassay; L-FABP, β2-microglobulin, and α1-microglobulin will be measured by latex agglutination turbidimetry; KIM-1 will be measured by an enzyme-linked immunosorbent assay; NAG will be measured by the artificial substrate MPT method.

### Adverse Events

All adverse events, including abnormal laboratory findings, will be collected and recorded in the electronic medical records with information on severity, seriousness, outcome, and the presence or absence of a causal relationship. The seriousness criteria for serious adverse events are (1) death, (2) life-threatening complication, (3) patient requires inpatient hospitalization or prolongation of hospitalization, (4) persistent or significant disability or incapacity, (5) risk of persistent or significant disability or incapacity, (6) congenital anomaly or birth defect, (7) and important medical event.

### Sample Size

The planned sample size includes 21 participants: 5 (24%) each in the 80 mg, 160 mg, and 240 mg flopropione cohorts and 6 (29%) in the control group. On the basis of the number of eligible patients in the previous year, anticipated consent rate, and screening dropouts, 21 participants are considered feasible to complete enrollment within 1 to 1.5 years.

Given the early-phase pilot nature of this study, the sample size is selected to balance between exploratory evaluation of potential dose-response trends, safety assessment, ethical considerations, and feasibility. Although not powered for statistical significance, 5 participants per dose level is considered appropriate for an initial exploration of a proof-of-concept study. Participants assigned to the control group will be enrolled among all cohorts and pooled for assessment, providing a common reference group for comparisons with each dose level. This approach allows for efficient use of control data while minimizing unnecessary patient exposure to the investigational intervention.

### Statistics

#### Analysis Set

##### Full Analysis Set

Patients in the control group are those who receive cisplatin, and participants in the flopropione group are those who receive flopropione. Data of participants in the flopropione group who do not receive flopropione are not included in the analysis.

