### Study Schedule

The schedule for informed consent, registration, randomization, observations, and assessments is presented in Table 1.

**Table 1 table1:** Study schedule.

Items	Before cisplatin administration		After cisplatin administration		
	From 28 d before cisplatin administration (before visit)	Cisplatin administration day (visit 1)	24 h later (visit 2)	48 h later (visit 3)	1 wk later (visit 4)
Allowable visit windows	—^a^	—	–2 h to +2 h	–2 h to +2 h	–36 h to +36 h
Consent acquisition and registration	✓^b^	✓^b^			
Patient background	✓^b^	✓^b^			
Cisplatin administration		✓			
Flopropione treatment		✓^c^	✓^c^		
Blood and urine collection	✓^b,d^	✓^b,d^	✓	✓	✓
Regimen name and concomitant therapy	✓^e^	✓^e^	✓^e^	✓^e^	✓^e^
Adverse events		✓^f^	✓^f^	✓^f^	✓^f^

^a^Not applicable.

^b^Conduct at either the before visit or visit 1.

^c^The first dose is taken 30 minutes before starting cisplatin administration. On the day of administration, a second dose is taken at least 4 hours apart. On the second day, 3 doses of 80 mg are taken at least 4 hours apart.

^d^Data are collected from 48 hours before cisplatin administration until before starting the regimen.

^e^Data collection period is from registration to 1 week after cisplatin administration.

^f^Data are collected from the start of flopropione treatment (or 30 minutes before starting cisplatin administration in the control group) until the 1-week evaluation point or until discontinuation. As much data as possible are collected at the discontinuation point. If adverse events persist, observation is continued until recovery or until the principal investigator or equivalent determines follow-up is unnecessary.

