### Eligibility Assessment

Eligibility will be confirmed within 28 days before cisplatin initiation. Baseline characteristics, including age, sex, height, weight, and comorbidities, will be recorded at registration.

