### Registration and Random Allocation

After confirming eligibility, registration and randomization will be performed through an electronic data capture system, assigning participants in a 5:2 ratio (flopropione:control) within each cohort.

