##### Per Protocol Set

This is the subset of the full analysis set that excludes participants who have deviations in drug administration or those who use prohibited concomitant medications.

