##### Safety Analysis Set

This set is the same as the full analysis set. The control group is evaluated as 1 group, and the flopropione group is stratified by dose.

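### The full analysis set uses a different exposure rule in each arm, so no planned set compares all randomised, cisplatin-treated participants as assigned

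*Protocol article*

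**What the plan says.** The rule is stated under Full Analysis Set: "Patients in the control group are those who receive cisplatin, and participants in the flopropione group are those who receive flopropione". The next sentence makes the exclusion explicit: "Data of participants in the flopropione group who do not receive flopropione are not included in the analysis".

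The other two sets are built on this one. Per Protocol Set: "This is the subset of the full analysis set that excludes participants who have deviations in drug administration", together with users of prohibited medication. Safety Analysis Set: "This set is the same as the full analysis set".

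On timing, Eligibility Assessment says "Eligibility will be confirmed within 28 days before cisplatin initiation", and Registration and Random Allocation says "After confirming eligibility, registration and randomization will be performed through an electronic data capture system". Allocation therefore comes before any dosing. Footnote c to the schedule in Table 1 says "The first dose is taken 30 minutes before starting cisplatin administration", so flopropione is taken before cisplatin starts.

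Analysis Method plans no formal hypothesis testing. It does plan between-group estimates for the biomarkers from mixed models, if feasible, and a Fisher exact test for AKI at each time point.

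**The concern.** Both entry conditions are events after randomisation, and they are different events. Randomisation makes the arms comparable only if people leave them by the same rule. Here a participant who receives cisplatin without flopropione counts if assigned to control and does not count if assigned to flopropione.

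Because the trial is open-label with an untreated control, only one arm has a study drug to refuse, miss or be unable to swallow. The reasons for missing it may be related to the risk of kidney injury. The per protocol set is a subset of the full analysis set and the safety set equals it, so neither brings the dropped participant back.

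What is at stake is the reading of the secondary biomarker results and the exploratory AKI proportions, which are meant to supply proof of concept for later trials.

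**Working it through.** **1. The plan's own figures.** Three cohorts at 5:2 give 3 × (5 + 2) = 21, with 15 on flopropione and 6 controls; 5/21 = 24% and 6/21 = 29%. This matches the Sample Size section. That section has no power calculation to reproduce. One participant is 1/5 = 20% of a dose group.

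**2. The entry rule applied to each case.**

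| What happens after randomisation | Assigned flopropione | Assigned control |
|---|---|---|
| Cisplatin started, flopropione taken as assigned | in | in (cisplatin only) |
| Cisplatin started, no flopropione | **out** | **in** |
| No cisplatin, but first flopropione dose taken | **in** | **out** (no cisplatin) |
| Neither drug | out | out |

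The second and third rows are asymmetric. The fourth is not: a participant whose cisplatin is called off before day 1 leaves either arm alike.

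**3. Size of the dropping route (second row).** Let p be the average event risk in the assigned group, q the risk of each dropped participant, n the group size and k the number dropped. With no drug effect:

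rate among those kept = (n·p − k·q)/(n − k), so shift = k(p − q)/(n − k).

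Take p = 30%, the cisplatin nephrotoxicity rate quoted in the Background (its use as the one-week AKI risk is an assumption), with n = 5 and k = 1:

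| q (assumed) | rate among the 4 kept | shift |
|---|---|---|
| 70% | (1.5 − 0.7)/4 = 20% | −10 points |
| 50% | (1.5 − 0.5)/4 = 25% | −5 points |
| 30% | (1.5 − 0.3)/4 = 30% | 0 |
| 10% | (1.5 − 0.1)/4 = 35% | +5 points |

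A negative shift favours flopropione. Over all 15 flopropione participants the same four values give −2.9, −1.4, 0 and +1.4 points. The plan, however, evaluates flopropione by dose level, so the figures for n = 5 are the relevant ones.

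**4. Size of the retention route (third row).** If a participant without cisplatin were counted as event-free, the expected rate would be p(n − k)/n. For n = 5 and k = 1 this is 0.30 × 4/5 = 24%, a shift of −6 points; for n = 15 it is 28%, a shift of −2 points. If p were 10%, the shift for n = 5 would be 0.10 × 1/5 = 2 points. This route always favours flopropione, but it needs the conditions discussed under the objection.

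**5. How likely is any case at all?** The article gives no expected rate of missed dosing. If each flopropione participant had an assumed 2%, 5% or 10% chance of being affected, the chance of at least one among 15 is 1 − 0.98^15 = 26%, 1 − 0.95^15 = 54% or 1 − 0.90^15 = 79%. For one dose group of 5 it is 10%, 23% or 41%.

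**6. Under one common rule.** If all randomised participants who start cisplatin are analysed as assigned, membership no longer depends on taking flopropione. The expected difference with no drug effect is then 0, provided that starting cisplatin is itself unrelated to the assigned arm.

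**The case against.** The strongest reply is that little may be lost. The trial is exploratory, is not powered, and plans no formal hypothesis testing. Oral dosing covers two days and participants are to receive cisplatin as inpatients. If everyone receives both drugs, the present and proposed sets contain the same people. All of this stands and lowers the severity. It does not remove the defect, because between-group estimates and a Fisher exact test are still planned and 5 per group cannot absorb a selective loss.

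Four stronger readings are tempting, and the documents do not support them.

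- **That the bias necessarily favours flopropione.** This does not follow for dropped participants. If frailer patients miss the dose, the shift favours flopropione. If low-risk patients decline the tablets, it goes the other way. If the reason is unrelated to risk, it is zero.
- **That retained participants without cisplatin are a main source of bias.** Cisplatin would have to be cancelled in the roughly 30 minutes after the first dose. The end points are also timed from cisplatin, so such a participant has no defined 24-hour, 48-hour or 1-week value. The 24% in step 4 holds only if that participant is nevertheless counted as event-free.
- **That the per protocol set can remove only flopropione participants.** Deviations in drug administration are not limited to flopropione in the text, and a control who takes non-study flopropione would also be removed.
- **That the safety set, and with it the primary end point, is wrongly defined.** Flopropione participants with at least one dose, by dose level, beside cisplatin-treated controls is a reasonable safety population. The fault lies in using that same population as the efficacy set.

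The interval of up to 28 days before cisplatin also adds little. Most changes of plan in that time would stop both drugs, and Table 1 allows registration on the day of cisplatin.

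**Conclusion.** The point holds for the efficacy comparison. The full analysis set has a different post-randomisation entry condition in each arm, and no planned set keeps all randomised, cisplatin-treated participants as assigned. The biomarker and AKI comparisons can therefore be biased, in a direction that the documents do not fix.

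The illustrative size is −10 to +5 points in a dose group of 5 for one dropped participant. It rests on an assumed 30% event rate, no drug effect and an individual risk between 70% and 10%. The 30% is a general rate with no stated time frame, and the Limitations section warns that nephrotoxicity may not appear after one administration, so these are orders of size and not predictions. If no dose is missed and nobody stops between the two drugs, the effect is nil.

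This should be fixed before database lock. It does not undermine the primary safety end point.

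**What to change.** For the biomarker and AKI analyses, define the full analysis set by one rule in both arms: all randomised participants who start cisplatin, analysed in the assigned arm and cohort whether or not flopropione was taken.

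Keep the present exposure-based definition for the safety set, stated in its own words rather than by reference to the full analysis set. Keep it also as a supportive as-treated analysis of the biomarkers and AKI. Report by arm and cohort how many participants the two definitions classify differently.

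The cost is a change of wording in the protocol or analysis plan. The set also needs outcome samples from cisplatin-treated participants who took no flopropione, on the visit schedule already planned. The statistical price is slight dilution of the estimated effect if someone does not take the drug. Registration was still open in January 2026, with the last participant due to finish by March 2026, so the change should be dated and justified before database lock.

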##### Per Protocol Set

This is the subset of the full analysis set that excludes participants who have deviations in drug administration or those who use prohibited concomitant medications.

##### Safety Analysis Set

This set is the same as the full analysis set. The control group is evaluated as 1 group, and the flopropione group is stratified by dose.

#### Analysis Method

As this is an exploratory pilot study, no formal hypothesis testing is planned. Descriptive and exploratory analyses will be conducted as mentioned subsequently.

The changes in urinary N-GAL, L-FABP, KIM-1, NAG, β2-microglobulin, and α1-microglobulin as well as serum creatinine, BUN, and estimated glomerular filtration rate from baseline to 24 hours, 48 hours, and 1 week after cisplatin administration will be assessed. Summary statistics will be calculated for the change amount, change rate, and observed values at each time point (24 hours, 48 hours, and 1 week after administration) relative to the baseline for each marker. Additionally, between-group differences will be estimated using mixed-effects models for repeated measures if feasible, following an assessment of the data distribution before database lock.

The proportion of participants meeting the CTCAE grade 1 or higher acute kidney injury criteria (creatinine level increase of 0.3 mg/dL or higher; creatinine 1.5 times above baseline) at 24 hours, 48 hours, and 1 week after cisplatin administration will be calculated. The number of participants meeting this criterion at each time point will be analyzed using Fisher exact test.

Nontargeted metabolome analysis will be conducted on serum and urine samples collected at each time point, following previously described protocols [20,21]. Briefly, metabolites will be extracted from the samples and analyzed using capillary electrophoresis coupled with time-of-flight mass spectrometry (Agilent 6210, Agilent Technologies). Metabolite identification will be performed by matching accurate mass-to-charge ratios (m/z) and migration times to the reference annotation table provided by Human Metabolome Technologies Inc. Peak areas obtained from the capillary electrophoresis coupled with time-of-flight mass spectrometry analysis will be normalized and expressed as relative concentrations to enable comparative evaluation across samples. Statistical analyses will include both univariable approaches and multivariable methods to identify significant temporal changes in the metabolome.

Differences in cancer type, cisplatin dose, renal function, and comorbidities may potentially influence the study end points. Therefore, to explore the impact of these baseline characteristics and clinical variables, subgroup analyses may be considered when deemed necessary.

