## Introduction

### Background

Nearly 5 decades have passed since cisplatin was approved in the United States in 1978, and it remains one of the most widely used and effective anticancer drugs worldwide [1]. Cisplatin exerts potent antitumor effects primarily through the formation of DNA cross-links, thereby inhibiting DNA replication and transcription. However, because its cytotoxic activity is not selective for cancer cells, cisplatin damages normal tissues and causes adverse effects, such as myelosuppression, ototoxicity, neurotoxicity, and nephrotoxicity, which often limit its clinical use [2]. Among these toxicities, nephrotoxicity is particularly significant as it can result in both acute and chronic kidney injury [3]. Cisplatin-induced nephrotoxicity (CIN) reportedly occurs in approximately 30% of the patients receiving cisplatin-based chemotherapy [4,5].

Hydration therapy can reduce the intratubular concentration of cisplatin, thereby lowering renal toxicity, and it is recognized as the globally established preventive method for CIN [6,7]. Particularly, recently developed short hydration protocols have offered comparable protective effects to conventional hydration while reducing patient burden and improving safety [8,9]. In addition, magnesium supplementation is used for preventing hypomagnesemia and mitigating the subsequent aggravation of renal dysfunction [10,11]. Use of osmotic diuretics, such as mannitol, has also been reported as a preventive strategy; however, their use might increase risk of nausea, vomiting, and potential deterioration in renal function, particularly in patients with comorbid diabetes mellitus or hypertension [12]. Although emerging preclinical evidence in animal and in vitro studies suggests that antioxidant-based agents, including riociguat, JP4-039, and amentoflavone, exert renoprotective effects against CIN, robust clinical data supporting their efficacy and safety are still lacking [13-15]. Thus, in addition to preventive strategies such as hydration therapy and magnesium supplementation, the development of novel prophylactic approaches for CIN is warranted.

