### Intervention

#### Intervention Procedure

Eligible participants are randomized in a 5:2 ratio per cohort to receive either flopropione (flopropione group) or no treatment (control group). Participants in the flopropione group receive oral flopropione twice on day 1 (30 minutes before cisplatin administration and at least 4 hours after) and 3 times on day 2. To ensure participant safety, a step-up dosing approach is applied. The single-dose levels are 80 mg in cohort 1, 160 mg in cohort 2, and 240 mg in cohort 3 on day 1. Progression to the next cohort will occur only after confirming safety in the preceding cohort. On day 2, all participants in the flopropione group will receive 80 mg per dose 3 times daily at intervals of at least 4 hours. Blood and urine samples will be collected within 48 hours before cisplatin initiation and at 24 hours, 48 hours, and 1 week after initiation. Participants in the control group undergo the same procedures as those in the flopropione group and receive standard cisplatin-based chemotherapy but without receiving flopropione. Regarding the analysis, participants assigned to the control group among all cohorts will be pooled for evaluation, whereas participants in the flopropione group will be evaluated according to their assigned dose level. An overview of the study procedure is shown in Figure 1; the step-up dosing approach diagram is shown in Figure 2.

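### The AKI counts get a Fisher exact test at each of three visits in a plan that disclaims formal testing; with 5 against 6 patients the p-values would carry almost no information, and exact intervals would serve better

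*Protocol article*

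**What the plan says.** All references are to the protocol article.

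- **Analysis Method** opens: "As this is an exploratory pilot study, no formal hypothesis testing is planned". It describes what follows as descriptive and exploratory.
- The same section says that the proportion of participants with CTCAE grade 1 or higher AKI "at 24 hours, 48 hours, and 1 week after cisplatin administration will be calculated". It continues: "The number of participants meeting this criterion at each time point will be analyzed using Fisher exact test". No significance level, sidedness or comparison groups are given for this test.
- **Intervention Procedure** says that "participants assigned to the control group among all cohorts will be pooled for evaluation", while flopropione patients are evaluated at their assigned dose level. **Safety Analysis Set** has the same structure, and **Sample Size** describes the pooled controls as the common reference for each dose level.
- **Sample Size** plans 5 patients at each of three dose levels and 6 controls, and states that the study is not powered for significance.
- **Exploratory End Points** lists AKI at each of the three visits, so AKI is neither primary nor secondary.
- **Background** gives the only event rate in the article: nephrotoxicity in "approximately 30% of the patients receiving cisplatin-based chemotherapy".

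**The concern.** The biomarkers and renal function measures are handled as the opening statement leads one to expect: summary statistics, and between-group differences estimated by a mixed model if feasible. AKI is handled differently. A Fisher exact test does not estimate anything; what it returns is a p-value against a null hypothesis. The section does not say how that p-value should be used or which groups it compares.

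With groups this small, the result is nearly settled in advance. Even complete protection would almost always give a non-significant p-value, repeated at three visits. In a study meant to supply proof of concept, such p-values can be mistaken for evidence that the drug has no effect on AKI. What a later trial needs is the observed proportion and a statement of how uncertain it is.

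**Working it through.** **Inputs**

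- Group sizes: 5 per dose level and 6 controls (Sample Size). Check: "assigning participants in a 5:2 ratio (flopropione:control) within each cohort", over three cohorts, gives 3×5 = 15 and 3×2 = 6, total 21, which matches the planned number. The article gives no power calculation to reproduce.
- Comparison: each dose level against pooled controls, 5 against 6. This is inferred from Intervention Procedure, Sample Size and Safety Analysis Set.
- Control AKI rate: 30%, an assumption taken from the nephrotoxicity figure in Background; 20% and 40% are also shown.
- Significance level: two-sided 0.05, an assumption.
- Effect: complete prevention, so the treated count is always 0. This is the most favourable effect possible and is an assumption.

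**Step 1. Which results reach p≤0.05?** With 0/5 treated and k/6 control events, the probability of the observed table is C(6,k)/C(11,k). The two-sided p-value adds the tables in the other tail that are no more probable.

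| Control events | Calculation | Two-sided p |
|---|---|---|
| 2/6 | (15+10)/55 | 0.455 |
| 3/6 | (20+10)/165 | 0.182 |
| 4/6 | (15+5)/330 | 0.061 |
| 5/6 | (6+1)/462 | 0.015 |
| 6/6 | 1/462 | 0.002 |

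At least 5 of 6 controls (83%) must have AKI. At 30%, 0.3×6 = 1.8 are expected, and 0/5 against 2/6 gives p = 0.455.

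**Step 2. How likely is that?** The treated count is fixed at 0, so the chance is the binomial probability of 5 or 6 events among 6 controls, 6π⁵(1−π) + π⁶:

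- π = 0.30: 6×0.00243×0.7 + 0.000729 = 0.0109, or 1.1%.
- π = 0.20: 6×0.00032×0.8 + 0.000064 = 0.0016, or 0.2%.
- π = 0.40: 6×0.01024×0.6 + 0.004096 = 0.0410, or 4.1%.

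If both groups have a 30% rate, full enumeration of the 5-against-6 tables gives an actual type I error of 0.65%.

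**Step 3. Other readings of the test, complete prevention, 30% control rate**

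| Reading | Control events needed | Chance |
|---|---|---|
| 5 against 6, one-sided 0.05 | 4/6 (p = 0.045) | 7.0% |
| 5 against 6, two-sided 0.10 | 4/6 (p = 0.061) | 7.0% |
| 5 against 6, two-sided 0.20 | 3/6 (p = 0.182) | 25.6% |
| Pooled 15 against 6, two-sided 0.05 | 3/6 (p = 20/1330 = 0.015; 2/6 gives 0.071) | 25.6% |
| Four-group exact test, 0.05 | 3/6 (p = 0.038; 2/6 gives 0.214) | 25.6% |

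The pooled comparison falls to 9.9% at a 20% control rate. The pooled and four-group rows assume complete prevention at all three dose levels.

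**Step 4. What an interval would show.** Exact 95% intervals are 0 to 52% for 0/5, 0 to 22% for 0/15 and 4 to 78% for 2/6. These show directly how little is known, which p = 0.455 does not.

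**The case against.** The strongest reply is that nothing here is concealed. The article rules out only formal testing, calls what follows exploratory, ranks AKI as an exploratory end point and says outright that the sample is not powered. Limitations adds that nephrotoxicity may not appear after a single administration. Exploratory p-values can sit beside a plan without confirmatory tests. All of this stands. A reader might infer a flat contradiction or a hidden claim of power; the documents support neither.

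Three further objections also limit the point:

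- A reader might infer that the test can never detect complete prevention. That is untrue: 0/5 against 5/6 or 6/6 would be significant. Such results are only very unlikely at the assumed rate.
- A reader might count nine tests, three doses by three visits. The section does not name the groups, so 5 against 6 is the natural reading but not a fixed one, and it is the least favourable of those examined at two-sided 0.05.
- A reader might treat the unmentioned confidence interval as an omission, or per-visit reporting as an error. An article can leave interval methods to the full protocol or analysis plan, and the per-visit proportions match the stated end point.

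The objections do not remove the affirmative choice of a significance test for AKI. An admitted lack of power is a reason to prefer estimation, and the Fisher sentence does not itself label its p-values as descriptive.

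**Conclusion.** The point holds as one of method and clarity for an exploratory end point. The article disclaims formal testing, then prescribes a test at three visits without naming the comparison. On the dose-level reading, that test has about a 1% chance of p≤0.05 under complete prevention, and about 26% on the pooled or four-group reading.

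These figures rest on a two-sided 0.05 level and a 30% control rate. The 30% describes nephrotoxicity in patients receiving cisplatin-based chemotherapy, not AKI at one visit in cycle 1. It is probably high for this use, given the caveat in Limitations and the restriction of each test to a single visit; a lower rate makes the chances smaller still. On any of these readings a non-significant result would say very little about whether flopropione affects AKI.

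**What to change.** Replace the Fisher exact tests with estimation:

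- At each visit, report AKI counts and proportions for each dose group and for pooled control, with exact 95% confidence intervals.
- Give an exact (unconditional) interval for the risk difference of each dose group against control.
- As supplementary summaries only, add any AKI through 1 week, and an interval for all flopropione (15) against control (6). The per-visit, by-dose presentation stays as the main one, because the end point and group structure are defined that way.

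If the tests are kept, the minimum is to name the groups compared and label the p-values as descriptive.

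The change is to the wording of the analysis. It needs no new data and adds no patient burden. The one cost is that no p-value is reported for AKI.
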